## Abstract

**Trial Registration::**

ClinicalTrials.gov, NCT05563103.

## Introduction

Walking deficits limit functional independence and increase comorbidities in nearly all persons with chronic (>1 year) spinal cord injury (SCI). Restoring the capacity for overground walking (e.g., speed and endurance) lowers healthcare costs for patients, their families, and caregivers and improves independence and quality of life. These are compelling reasons why reducing deficits in walking remains a high priority for many with SCI.^1^ Even minor improvements in walking that enable a person to walk independently within their community safely and efficiently may translate into significant health advantages. Given that there is no known cure for SCI and no single treatment is sufficient to overcome walking deficits, there is a tremendous need for targeted therapies that boost walking recovery for persons living with chronic SCI.

Combining treatments that harness endogenous mechanisms of plasticity shows promise in improving functional recovery after SCI. In particular, repetitive exposures to modest bouts of low oxygen (therapeutic acute intermittent hypoxia; tAIH) elicit remarkable neural plasticity through *de novo* synthesis of brain-derived neurotrophic factor (BDNF)-dependent signaling cascades^2^ that strengthen synaptic pathways to respiratory motor neurons in rodent SCI models.^3,4^ Lovett-Barr and colleagues showed that daily (7 consecutive days) tAIH before ladder walking practice improved forelimb stepping and breathing capacity in rodents with chronic, incomplete SCI.^5^ Since then, several randomized controlled trials showed that repetitive (up to 14 sessions) tAIH elicited similar training-related improvements in walking in persons with chronic (>6 months), incomplete SCI.^6–8^ Hayes and colleagues found that 5 consecutive days of tAIH + WALK improved overground walking endurance, but tAIH alone did not.^6^

These studies provide a conceptual framework to support the possibility that tAIH primes residual spinal circuitry after SCI and “boost” the functional benefits of task-specific training. Using tAIH as a primer for other promising treatments that target similar mechanisms of spinal plasticity may help overcome constraints on the rate and duration of motor recovery after chronic SCI.

tAIH may enhance the neuromodulatory effects of transcutaneous spinal stimulation (tSTIM) on restoring walking after SCI. tSTIM may engage spared afferent pathways and descending supraspinal signaling to excite spinal interneurons and motor neurons closer to their firing threshold.^9^ Clinical case reports involving persons with severe paralysis show that epidural electrical stimulation can elicit voluntary muscle activity and bipedal stepping.^10–12^ Concurrent application of repetitive (2 weeks) tSTIM combined with skill-based walking practice (WALK_tSTIM_) enhanced training-related gains.^13–15^ However, these studies showed that many of the reported improvements in overground walking required months of training to achieve functionally meaningful gains. One possible explanation is that plasticity wanes with time, such that those with chronic SCI experience limited training-related improvements.^16^

We speculate that repetitive tAIH and WALK_tSTIM_ act synergistically, so the combination of these modalities may further enhance training-related gains in walking function. Although the exact neural mechanisms and dosing for tAIH- and tSTIM-induced facilitation in walking performance are not fully understood in humans, there is ample pre-clinical evidence that repetitive exposures to these therapies trigger rapid changes in functional connectivity within and between the brain and spinal cord structures.^4,17,18^ Thus, this clinical trial protocol aims to explore the safety and efficacy of tAIH pre-treatment to WALK_tSTIM_ in restoring functional walking for persons with chronic SCI.

### Hypothesis and aims

This study aims to expand tAIH's therapeutic “reach” as a pre-treatment for restoring function in persons with chronic SCI. Specifically, we propose to combine tAIH, transcutaneous spinal stimulation, and task-specific training to maximize function in spared neural pathways. Using an established tAIH protocol known to elicit improvement of walking ability in persons with chronic spinal injuries,^6^ we first propose to investigate the potential of tAIH (2 weeks) as a pre-treatment to WALK_tSTIM_ to elicit faster (potency) and persistent gains (efficacy) in walking for persons with chronic SCI (Fig. 1). We hypothesize that tAIH + WALK_tSTIM_ will boost the enduring effects of training-related walking improvements in persons with chronic SCI (Aim 1, efficacy). We also aim to determine the minimal number of combinatorial sessions needed to achieve a minimal clinically important difference (MCID) in walking improvements (Aim 2, potency) without eliciting maladaptive changes (Aim 3, safety).

**FIG. 1. f1:**
[figure not shown]
Illustration of study hypotheses. We hypothesize that the combination of tAIH + WALK_tSTIM_ will result in larger, more persistent improvements (increase in efficacy) in walking speed than tAIH + WALK_tSHAM_ or Placebo + WALK_tSTIM_. Additionally, we hypothesize that tAIH + WALK_tSTIM_ will result in fewer training sessions to achieve an MCID in walking speed improvements (greater potency) compared to Placebo + WALK_tSTIM_ or tAIH + WALK_tSHAM_. MCID, minimal clinically important difference; tAIH, therapeutic intermittent hypoxia; WALK_tSTIM_, transcutaneous spinal stimulation-enhanced walking therapy.

These aims will be the first to investigate the safety and efficacy of tAIH priming with WALK_tSTIM_ to augment walking recovery in persons with chronic SCI. Determining how to harness these potentially synergistic treatments may lead to meaningful recovery that profoundly impacts the lives of persons with SCI while establishing more potent therapeutic strategies as a part of “best practices in SCI care.”

## Methods

### Study design

In this double-blinded, placebo-controlled, randomized controlled trial (ClinicalTrials.gov identifier: NCT05563103), we are examining the efficacy, potency, and safety of repetitive tAIH before WALK_tSTIM_ in a cohort of adults with chronic SCI in two tertiary hospitals: Spaulding Rehabilitation Hospital (Cambridge, MA) and Shirley Ryan AbilityLab (Chicago, IL). The Mass General Brigham (MGB) Institutional Review Board (IRB) approved the study protocol following the Declaration of Helsinki. Recruitment and enrollment of the study commenced in January 2023.

### Sample size

We plan to enroll *N* = 60 persons with chronic, incomplete SCI in this clinical trial. We created a Consolidated Standard of Reporting Trials (CONSORT) flow diagram (Fig. 2) to summarize our trial enrollment, intervention, allocation, follow-up, and analyses.^19^ The initial sample size is an estimate from conservative power calculations on preliminary data that support our hypotheses testing in Aims 1 and 2.

**FIG. 2. f2:**
[figure not shown]
Flow diagram of anticipated subject recruitment, enrollment, intervention allocation, and disposition status. We anticipate *N* = 48 people with SCI to complete the study. SCI, spinal cord injury; tAIH, therapeutic intermittent hypoxia; WALK_tSTIM_, transcutaneous spinal stimulation-enhanced walking therapy.

For Aim 1, our sample-size estimate focused on results from an earlier placebo-controlled clinical trial that reported that persons with incomplete SCI completed the 10-Meter Walk Test (10MWT) faster after tAIH + WALK (−4.3 ± 1.0 sec, faster relative to baseline) as compared to Placebo + WALK (0.9 ± 0.4 sec, slower relative to baseline).^6^ From these results, we conservatively estimated the standard deviation of the 10MWT time relative to baseline as 2.0 sec in Placebo + WALK_tSTIM_ and tAIH + WALK_tSHAM_ and 3.0 sec in tAIH + WALK_tSTIM_. The estimated difference between the change in tAIH + WALK_tSTIM_ and the change in Placebo + WALK_tSTIM_ was −5.2 sec, and that difference between tAIH + WALK_tSTIM_ versus tAIH + WALK_tSHAM_ was estimated as −3.14 sec. Assuming a 20% dropout rate with 16 completers per group, three outcome measures (10MWT, Timed Up and Go Test [TUG], and the 6-Minute Walk Test [6MWT]), and a significance level of 0.0167 adjusted for the three repeated outcomes,^20^ this study will have >99% statistical power in comparing tAIH + WALK_tSTIM_ versus Placebo + WALK_tSTIM_ and >81% statistical power in comparing tAIH + WALK_tSTIM_ versus tAIH + WALK_tSHAM_.

For Aim 2, our sample-size estimate focused on results from a preliminary crossover study (unpublished) that showed that *N* = 3 people with incomplete SCI improved their walking speed after 5 consecutive days of tAIH + WALK_tSTIM_. Two participants achieved an MCID on their 10MWT at post-treatment day 5. However, no participants achieved an MCID after 5 consecutive days of Placebo + WALK_tSTIM,_ where the maximum increase in speed corresponded to 0.03 m/s. We predict that participants will require at least seven sessions of Placebo + WALK_tSTIM_ to achieve an MCID in walking speed. Using bootstrap sampling with replacement, we estimated the standard deviation for the number of sessions to achieve an MCID from our pilot study to be 1.5 days. Assuming that seven Placebo + WALK_tSTIM_ sessions are needed in order to achieve MCID as compared to five tAIH + WALK_tSTIM_ sessions estimated from our pilot data, the statistical power is >95% to detect the group difference to achieve an MCID on the 10MWT, with the sample sizes of 16 per group after 20% dropout.

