### Statistical analysis

We plan to test three subhypotheses using parametric and non-parametric statistical inference methods. Statistical significance corresponds to a *p* value <0.05.

#### Hypothesis 1

Daily tAIH + WALK_tSTIM_ enhances overground walking ability in persons with chronic SCI compared to tAIH + WALK_tSHAM_ or Placebo + WALK_tSTIM_.

We predict a decrease in 10MWT and TUG time and an increase in 6MWT distance relative to baseline after tAIH + WALK_tSTIM_ (vs. Placebo + WALK_tSTIM_, tAIH + WALK_tSHAM_). We quantify walking ability using three outcome measures: change in TUG, 10MWT, and 6MWT relative to baseline assessments. Change in performance on these measures will occur after the last intervention session and again at 1-, 4-, and 12-week post-intervention follow-ups (Fig. 3). We will test three related subhypotheses using a linear mixed model with intervention (tAIH + WALK_tSTIM_, tAIH + WALK_tSHAM_, and Placebo + WALK_tSTIM_) and time (visit number) as the fixed main effects, with subject as random effect, whereas scores for TUG (time), 10MWT (time), and 6MWT (distance) will be considered as repeated measures.^56^

Differences from assessment after completion of the walking practice sessions will be compared between and within interventions at tests (T_1_, T_2_) and follow-ups (1, 4, and 8 weeks post-intervention). If analyses of variance (ANOVAs) reveal significant differences, the Tukey-Kramer *post hoc* test will identify pair-wise differences. If walking performance measures at the end of the walking practice sessions are significantly different between intervention groups, we will use an analysis of covariance. We also plan to fit a linear mixed model to test the magnitude and duration of tAIH priming effects based on linear contrasts after controlling for the study period, baseline primary outcomes, and demographics data.

#### Hypothesis 2

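### Aim 1 is powered for one test per outcome at 0.0167, but Hypothesis 1 describes a single mixed model with three walking scores on different scales as its repeated measures, judged at p <0.05

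*Protocol article*

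**What the plan says.** **Protocol article, Methods, Sample size (Aim 1 paragraph, after the Figure 2 legend).** Power is computed on 10MWT change only. The standard deviations are given as "conservatively estimated the standard deviation of the 10MWT time relative to baseline as 2.0 sec" for the two comparator arms and "3.0 sec in tAIH + WALK_tSTIM" for the combination arm. The difference from Placebo + WALK_tSTIM is −5.2 s. The difference from tAIH + WALK_tSHAM "was estimated as −3.14 sec". With 16 completers per group the text uses "a significance level of 0.0167 adjusted for the three repeated outcomes" and claims power above 99% and above 81%.

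**Protocol article, Statistical analysis, opening lines.** "Statistical significance corresponds to a *p* value <0.05". The 0.0167 level does not appear in this section.

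**Protocol article, Statistical analysis, Hypothesis 1.** The prediction is made outcome by outcome: "We predict a decrease in 10MWT and TUG time and an increase in 6MWT distance relative to baseline". Three linked subhypotheses are then to be tested with a linear mixed model, in the singular. Intervention and visit number are its fixed main effects and subject is its random effect, and "scores for TUG (time), 10MWT (time), and 6MWT (distance) will be considered as repeated measures". No outcome factor, outcome-by-intervention term or standardization of scores is listed.

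**The concern.** Two things fail to match between the sample-size text and the analysis text.

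The first is the model. A level of 0.05/3 belongs to a plan that yields a separate inference for each outcome. The model sentence makes the scores themselves the within-subject repeats and gives the model nothing that separates one outcome from another. An analyst who followed it to the letter would stack seconds and metres in one response column and report one intervention effect. Improvement is negative on two of those scales and positive on the third, so that effect has no clinical meaning and its sign need not indicate benefit. Another analyst would fit three models. Both could claim to have followed the protocol.

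The second is the level. The only threshold in the analysis section is 0.05. An analyst working from that section alone would test three primary outcomes without the adjustment on which the trial was powered.

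**Working it through.** **1. The plan's own figures.** Inputs from the Sample size section: n = 16 per arm, SDs 3.0 and 2.0 s, differences 5.2 and 3.14 s, alpha 0.0167. Sidedness is not stated; two-sided is assumed.

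- Alpha: 0.05/3 = 0.0167.
- Standard error = √(3.0²/16 + 2.0²/16) = √(13/16) = 0.901 s.
- Welch degrees of freedom = (13/16)² / [((9/16)² + (4/16)²)/15] = 26.1. The two-sided critical value at 0.0167 is 2.557.
- Noncentrality: 5.2/0.901 = 5.77 and 3.14/0.901 = 3.48.
- Power (noncentral t): 99.9% and 81.5%. These match the stated >99% and >81%.
- Dropout: 16/(1 − 0.20) = 20 per arm, as planned.

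At alpha 0.05 the 3.14 s comparison would have 91.8%. The stated 81% therefore belongs to a test on one outcome at 0.0167.

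**2. Familywise error, counting one test per outcome and assuming independence.**

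- At 0.0167 each: 1 − (1 − 0.05/3)³ = 4.9%.
- At 0.05 each: 1 − 0.95³ = 14.3%.

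**3. What the literal model would estimate.** With balanced data, a random subject intercept and no outcome term, the arm effect is the difference in subject means over all stacked rows. For one time point it is (Δ10MWT + ΔTUG + Δ6MWT)/3. The article gives only the 10MWT values. The following are assumptions:

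- TUG has the same difference (−3.14 s) and SDs as the 10MWT.
- The 6MWT change SD is 20 to 40 m.
- Correlations are either 0 or 0.6 in size, negative between times and distance.

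Simulated rejection rates for the pooled effect at 0.05, 16 per arm:

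| Assumed 6MWT difference | Pooled effect (mixed units) | Rejection |
|---|---|---|
| 0 m | (−3.14 − 3.14 + 0)/3 = −2.09 | 7% to 17% |
| +6.28 m | (−3.14 − 3.14 + 6.28)/3 = 0 | about 5% |
| +20 m | (−3.14 − 3.14 + 20)/3 = +4.57 | 15% to 58% |

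The rows show dilution, exact cancelling, and a positive sign set by the metres. A separate 10MWT test at 0.0167 keeps its 81.5% in every row.

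The metres also dominate the noise. In the combination arm with a 6MWT SD of 30 m and independent errors, 900/(9 + 9 + 900) = 98% of the variance of the stacked sum comes from the 6MWT.

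**4. Holm against Bonferroni.** If all three outcomes carried the 3.14 s planning effect on the 10MWT scale (an assumption), simulation at between-outcome correlations of 0.3, 0.6 and 0.8 gives average per-outcome power of about 81% with Bonferroni and 89%, 88% and 87% with Holm.

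**The case against.** The strongest reply is that nobody intended a pooled model. Hypothesis 1 announces three subhypotheses, which matches three outcomes. It predicts a direction for each, and it lists visit number as a fixed effect, so visits are already a repeated dimension. Under Hypothesis 3 the same idiom is applied to six unrelated scales (SCATS, NPRS, CVLT, O-TMT, NBDS, NBSS), which can hardly be meant as one response. On that view, scores called repeated measures are simply scores measured repeatedly, and 0.0167 confirms testing by outcome. The model sentence is also visibly condensed: it lists no intervention-by-time term, although arms are to be compared at each visit. Finally, 0.0167 does not require three models, because outcome-specific contrasts in one joint model could be tested at that level.

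Most of this stands. A reader might infer that the trial will pool seconds and metres, or that gains of opposite sign will cancel. The document does not establish either. Pooling is one reading of the sentence, and exact cancelling needs a 6MWT gain equal to the sum of the two timed gains, here an assumed 6.28 m. A reader might also infer that the sample size is wrong; it is not.

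The reply does not remove the mismatch. The article states a model, so this is not a matter silently left to a fuller document. The sample-size text also calls the outcomes, not the visits, repeated. No outcome-specific contrasts are described. The gap between 0.0167 and p <0.05 remains on every reading.

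**Conclusion.** The point holds as an ambiguous primary model combined with an inconsistent significance level. The per-outcome reading is plausible and agrees with the power calculation, but the sentence as written does not specify it, and the literal alternative gives an effect that cannot be interpreted.

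The firm numbers are the reproduced power and the familywise error of 4.9% against 14.3%, the latter for independent outcomes. The three walking tests are probably correlated, so the actual inflation at 0.05 each would probably be smaller. The rejection rates for the pooled model are illustrations that rest on assumed TUG and 6MWT values. They show the kinds of failure possible, not a forecast for this trial. The correction is worth making before analysis, because it decides what the primary test is.

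**What to change.** In Statistical analysis, Hypothesis 1, replace the model sentence with: one linear mixed model for each of 10MWT, TUG and 6MWT, with that outcome's visits as the repeated measures within subject.

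In the same place, state that the three outcomes are tested as a family at overall 0.05, and make the general p <0.05 statement subject to this. Either of two rules will serve:

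- 0.0167 for each outcome, exactly as powered; or
- Holm's step-down procedure, which is never less powerful than Bonferroni at the same familywise error. Its small downside is that matching confidence intervals are less simple. The choice is optional and the correction does not depend on it.

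In Sample size, delete the word that calls the three outcomes repeated.

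The cost is wording only. No extra data are needed, and the plan stays at 16 completers and 20 randomized per arm.

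### The >81% power for the combination versus tAIH + WALK_tSHAM fits a two-group t-test at 0.0167; Tukey-Kramer, the pairwise test named, has about 78% at that level

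*Protocol article*

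**What the plan says.** The Sample size section of the protocol article (Aim 1) bases power on the change in 10-Meter Walk Test time. It sets standard deviations of "2.0 sec in Placebo + WALK_tSTIM_ and tAIH + WALK_tSHAM_ and 3.0 sec in tAIH + WALK_tSTIM". It takes a difference of −5.2 s against Placebo + WALK_tSTIM, and states "that difference between tAIH + WALK_tSTIM_ versus tAIH + WALK_tSHAM_ was estimated as −3.14 sec". The numbers are given as "Assuming a 20% dropout rate with 16 completers per group", with "a significance level of 0.0167 adjusted for the three repeated outcomes". From these it reports more than 99% power for the first comparison and ">81% statistical power in comparing tAIH + WALK_tSTIM_ versus tAIH + WALK_tSHAM" for the second. It does not name the test behind either figure.

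The Statistical analysis section says "Statistical significance corresponds to a *p* value <0.05" and does not repeat 0.0167. Under Hypothesis 1 it plans a linear mixed model over the visits. The pairwise step begins "If analyses of variance (ANOVAs) reveal significant differences, the Tukey-Kramer", and that post hoc test is to identify the pairwise differences. Hypothesis 1 itself names two comparisons: the combination against each of the other two groups.

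**The concern.** The level 0.0167 is 0.05/3, spent on three outcomes (10MWT, TUG, 6MWT). Nothing in it pays for three pairwise group comparisons. Tukey-Kramer does make that payment, through a larger critical value, and it also covers Placebo + WALK_tSTIM versus tAIH + WALK_tSHAM, about which Hypothesis 1 predicts nothing. If the power was computed without this payment, the stated figure does not describe the named test at the stated level.

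At stake is the harder of the two key contrasts, the one that shows what stimulation adds to tAIH. The stated margin above 80% is thin, so a small loss takes it below.

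**Working it through.** **Inputs**, all from Sample size (Aim 1): differences 3.14 s and 5.2 s; SD 3.0 s in the combination group and 2.0 s in each comparator; 16 completers per group; level 0.0167. Sidedness is not stated. Two-sided is assumed because it reproduces the stated figure.

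**1. The plan's own figure.**
- Standard error of the difference: √(3²/16 + 2²/16) = √(13/16) = 0.901 s.
- Noncentrality: 3.14/0.901 = 3.48.
- Pooled two-group t-test, 30 df, critical value 2.53: power 82.2%.
- Welch test: df = (13/16)² / [((9/16)² + (4/16)²)/15] = 26.1, critical value 2.56, power 81.5%.
- For 5.2 s: 5.2/0.901 = 5.77, power 99.9%.

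Both stated figures are reproduced. Other readings fit less well: a normal approximation gives 86% and a one-sided t-test about 89%.

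**2. Tukey-Kramer at the same level.**
- With three groups, 45 df (3 × 15) and level 0.0167, the studentized range quantile is 4.063, so the critical value is 4.063/√2 = 2.87.
- Tukey-Kramer uses the error variance pooled over all three groups: (9 + 4 + 4)/3 = 5.67.
- In 400,000 simulated trials with SDs 3, 2 and 2, power for 3.14 s was 78.3%. Requiring a significant ANOVA first at the same level did not change it.
- The 5.2 s contrast stayed above 99%.

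This is a favourable figure. Pooling gives the pair a variance of 2 × 5.67/16 = 0.71, whereas its true value under the plan's SDs is 13/16 = 0.81.

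**3. Tukey-Kramer at p < 0.05.** The critical value falls to 2.42 and simulated power for 3.14 s is 88.4%.

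**4. The two comparisons of Hypothesis 1 in fixed order.** The combination is tested first against Placebo + WALK_tSTIM, then against tAIH + WALK_tSHAM, each by a Welch test at 0.0167. The first step almost always succeeds under the plan's assumptions, so power for the second is essentially that of the single Welch test, about 81%.

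**5. Alternatives that look better but do not hold.** A pooled-variance Dunnett test (critical value 2.74) shows about 82%, and a pooled-variance fixed-order test about 87%. The combination group, which has the larger SD, is in both comparisons, so pooling understates both standard errors. With no true differences and SDs 3, 2 and 2, the Dunnett familywise error is about 0.025 instead of 0.0167. The pooled fixed-order test has the same fault, with an error of about 0.025 on its first step.

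| Test for the 3.14 s contrast | Level | Power |
|---|---|---|
| Two-group t-test (pooled / Welch) | 0.0167 | 82.2% / 81.5% |
| Tukey-Kramer | 0.0167 | 78.3% |
| Tukey-Kramer | 0.05 | 88.4% |
| Fixed order, Welch | 0.0167 | about 81% |

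**The case against.** Four points can be made for the plan.

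- **The arithmetic is right.** On its own inputs the figure is correct for a two-group t-test. This stands. The mismatch is between the power calculation and the named pairwise test, and the t-test is itself inferred from the match.
- **The analysis section says p < 0.05.** At that level Tukey-Kramer exceeds the stated power. This stands as arithmetic. A reader might therefore infer either that the planned test certainly has less than 80% power, or that no problem exists. The document supports neither, because it does not say which level governs the pairwise tests. The power claim is made at 0.0167, and 0.05 for each of three outcomes gives up the adjustment on which that claim rests.
- **The planned model is richer than a single-visit comparison.** Repeated visits and baseline covariates could raise power. If covariates correlated 0.25 with the change (an assumption; no correlation is given), Tukey-Kramer at 0.0167 would return to about 81%, and at 0.4 to 86%. This stands as a limit on the 78%. The document claims no such gain, and its own figure matches a single-visit comparison without covariates.
- **The gap is small.** It is about 3 points, and the SDs are described as conservative estimates. This stands, and it sets the weight of the point.

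**Conclusion.** The stated power holds for a two-group t-test at 0.0167. Tukey-Kramer at that level has about 78% for the 3.14 s contrast and more than 99% for the 5.2 s contrast. This assumes two-sided testing, one visit, no covariates, normal data and the plan's own SDs and completer numbers.

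It is a minor correction. A reader might infer that the trial is underpowered or needs more patients, but the document does not support that: the loss is small, confined to one contrast, and could be offset by the planned model. What needs settling is that the two sections give different levels, and that the power figure belongs to a test other than the one named for the pairs.

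**What to change.** State in the Statistical analysis section that each of the three primary outcomes is tested at 0.0167. Then do one of the following:

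- **Keep Tukey-Kramer** and restate the power for the combination versus tAIH + WALK_tSHAM as about 78%, noting that this is for a single visit without covariates.
- **Replace Tukey-Kramer for Hypothesis 1** by its two named comparisons in fixed order: the combination versus Placebo + WALK_tSTIM first, then versus tAIH + WALK_tSHAM, each with a Welch test at 0.0167. This keeps about 81%.

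Either choice costs about a sentence and no additional patients. Under the second, Placebo + WALK_tSTIM versus tAIH + WALK_tSHAM becomes descriptive, and the second comparison can be claimed only if the first succeeds.

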### Randomization

Before enrolling the first study participant, a research statistician generated the balanced randomization scheme for treatment allocation at both clinical sites using the R Statistical Package.^21^ This method randomly assigns participants to one of three intervention groups (*N* = 20 per group): 1) tAIH + WALK_tSTIM_, 2) tAIH + WALK_tSHAM_, and 3) Placebo + WALK_tSTIM_ in blocks of 6 participants. Using this scheme, the site coordinator will assign each participant to their respective intervention group in the order in which they complete the walking practice sessions. Although the coordinator informs participants about their possible group assignment, they will be blinded to the treatment they receive (i.e., tAIH or Placebo, WALK_tSTIM_, or WALK_tSHAM_). The clinical raters and trainers will also be unaware of each participant's treatment assignment. Based upon reports from participants blinded during our previous tAIH study,^6^ >75% guessed incorrectly or were uncertain of the breathing intervention received, suggesting that our previous blinding and air delivery methods were effective.

We plan a similar integrity analysis for the stimulation sham protocols (no stimulation). Participants guess the interventions received at the end of each treatment session and indicate their guess confidence using a Likert scale.^22,23^ Using a contingency table and Fisher's exact test, we will determine whether the probability of correct guessing differs from chance.

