### Study limitations

Clinical trials are necessary for the study of combinatorial interventions to treat SCI. However, the experimental protocols for these trials are often beset with study design challenges attributable, in part, to confounding treatment interactions, small sample size, short study duration, and SCI heterogeneity. The study of multiple treatments and their interactions requires the appropriate choice of controls to discriminate between the clinical outcome of the treatments alone, combined, or neither. Identifying the study groups is pivotal to trial success, but requires larger sample sizes. Because of challenges from the ethical perspective in SCI research with humans, we cannot include a control (no treatment) group in the present trial. We anticipate that some participants will receive additional therapy services upon study enrollment.

We will quantify the interactions between frequency/duration of these services and our primary outcome measures. The biostatistician also will use multi-variate statistical models to assess these and other potential confounds to our outcome measures. Though most studies continue for longer periods (e.g., 12 weeks),^61^ up to eight sessions of tAIH or WALK_tSTIM_ are sufficient to elicit improvements in walking speed in persons with SCI.^6,8,62^ To consider the potential long-term effects of tAIH + WALK_tSTIM_ on walking ability, we will follow up at 1, 4, and 8 weeks post-treatment.

Small sample sizes can undermine the translation of results to the larger heterogeneous patient population. We also acknowledge that balancing treatment groups of a heterogeneous SCI cohort will be a challenge. To address this obstacle, we will consider age, sex, reliance on walking aids,^63^ and injury level. Second, we do not yet know the potency of WALK_tSTIM_ and eight sessions may be considered too few to achieve MCID in the treatment groups. We chose eight sessions to remain pragmatic in treatment duration while aligning our study design to a recent placebo-controlled trial that found WALK_tSTIM_ induced clinically significant gains in walking speed within six sessions.^62^ We acknowledge that achieving MCID in eight sessions may not occur during treatments without tAIH. If this happens, we will compare groups using survival-type analyses to include those with no participants who achieved MCID.^64^ Third, medication changes are frequent in persons with SCI, which may alter neural plasticity.

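### The Aim 2 power of more than 95% holds at exactly seven versus five sessions with every participant's time observed; the documents do not firmly support those inputs, and power should be given as a range for a censored time-to-MCID test

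*Protocol article*

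**What the plan says.** The Aim 2 calculation is in Methods, Sample size. It draws on an unpublished crossover pilot in three people. On the combination, two of the three reached the MCID on the 10MWT at day 5. On Placebo + WALK_tSTIM none did after five days. The control value is then predicted: "We predict that participants will require at least seven sessions of Placebo + WALK_tSTIM_ to achieve an MCID in walking speed". The calculation takes that lower bound of seven as the control mean, sets it against a combination mean of five drawn from the pilot, and uses a spread obtained by bootstrap: "we estimated the standard deviation for the number of sessions to achieve an MCID from our pilot study to be 1.5 days". The result is that "the statistical power is >95% to detect the group difference to achieve an MCID on the 10MWT". This assumes 16 completers in each arm once a fifth have been lost. The opening of the same section describes the power calculations behind Aims 1 and 2 as conservative.

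Three other places bear on this:

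- **Statistical analysis, Hypothesis 2** takes the number of sessions needed to reach the MCID, out of eight, as the outcome of a linear mixed model, with group and baseline speed as fixed effects.
- **Study limitations, length of course.** The eight-session course is justified by a placebo-controlled trial that "found WALK_tSTIM_ induced clinically significant gains in walking speed within six sessions".
- **Study limitations, caveats.** The same paragraph says that the potency of WALK_tSTIM is not yet known and that the MCID may not be reached in eight sessions without tAIH. In that event, survival-type methods would be used.

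**The concern.** A single power figure with no range tells the reader that Aim 2 is almost certain to detect a potency difference. It depends on a two-session gap that the pilot did not measure. The control time lies beyond the end of pilot observation, and the combination time is incomplete for one of three people. The trial cited for the length of the course suggests that stimulation with walking practice may work sooner than the power calculation assumes.

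The calculation also treats every participant as having an observed session count. The trial stops counting at eight, and the plan's own mean and SD put a noticeable share of controls beyond that point. If Aim 2 came out null, the stated power would invite the conclusion that tAIH adds no potency, when the trial may only have been unable to show it.

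**Working it through.** **Inputs** (Sample size, unless noted): control mean 7, combination mean 5, SD 1.5, completers per arm 20 × 0.8 = 16. The 20 per arm is in Randomization: "randomly assigns participants to one of three intervention groups (*N* = 20 per group". The significance level is 0.05 (Statistical analysis). Sidedness is not stated; two-sided is assumed.

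**Step 1: reproduce the stated figure.** For a two-sample t-test with n = 16 per arm and 30 degrees of freedom:

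- Standard error = SD × √(2/n) = 1.5 × √(2/16) = 0.530.
- Noncentrality = difference / 0.530 = 2 / 0.530 = 3.77; critical value 2.042.
- Power = 95.4% (normal approximation 96.5%). This reproduces the claim.

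**Step 2: vary the control mean, all else fixed.**

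| Control mean | Difference | Noncentrality | Power |
|---|---|---|---|
| 6 | 1 | 1.89 | 44.6% |
| 6.5 | 1.5 | 2.83 | 78.1% |
| 7 | 2 | 3.77 | 95.4% |
| 8 | 3 | 5.66 | above 99.9% |

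The smallest difference with 95% power is 1.98 sessions, so there is almost no room below two. A slower combination arm has the same effect: 5.5 against 7 is a difference of 1.5, again 78%. With a one-sided 0.05 test, the figure at a control mean of six is about 58%.

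**Step 3: vary the SD, keeping 7 versus 5.** SD 2.0 gives 78%; SD 2.5 gives 59%.

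**Step 4: how many controls would not reach the MCID by session 8?** With mean 7 and SD 1.5, taken as normal:

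- Counts rounded to the nearest session: 1 − Φ((8.5 − 7)/1.5) = 1 − Φ(1.00) = 15.9%.
- Counts rounded up: 1 − Φ((8 − 7)/1.5) = 1 − Φ(0.67) = 25.2%.

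That is about 2.5 to 4 of 16 controls. In the combination arm the same formulas give 1.0% and 2.3%.

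**Step 5: what this does to power** (simulation, same means and SD, counts in whole sessions, two-sided 0.05; ranges cover the two rounding rules):

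| Handling of non-achievers | 6 vs 5 | 6.5 vs 5 | 7 vs 5 | 8 vs 5 |
|---|---|---|---|---|
| Kept, scored as 9, t-test | 43% | 75–76% | 95% | about 100% |
| Censored at session 8, log-rank | 41% | 73% | 93% | above 99% |
| Dropped, t-test on the rest | 34–38% | 59–67% | 79–86% | 89–97% |

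The cap itself costs little if non-achievers stay in the comparison. Dropping them costs about 10 to 16 points at the design values, because it removes the slowest participants mainly from the control arm.

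**The case against.** **The stated power is correct for its inputs and openly conditional on them.** This stands. A reader might infer an arithmetic error; there is none.

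**Study limitations does not contradict the prediction of seven.** This largely stands. A clinically significant gain within six sessions in another trial is not a mean of six sessions to the MCID. A group gain or a subset of responders by session six is compatible with a mean of seven. The article does not give that trial's threshold, responder share or reference point. Here stimulation also starts after eight walking-practice sessions, so comparability is unknown. The two statements sit uneasily together, but no more than that.

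**The uncertainty runs both ways.** This stands too. Seven was put forward as a minimum, no pilot participant exceeded a 0.03 m/s gain on Placebo + WALK_tSTIM, and Study limitations allows for controls who need more than eight sessions. Slower controls would raise power, provided that those who never reach the MCID are kept in the analysis. Adjusting for baseline speed could also help, but the article gives no correlation from which to size that.

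**A survival-type analysis is already foreseen.** Only in part. It is a fallback, triggered if the MCID is not reached without tAIH. The main model is left without a defined outcome for non-achievers, and the method would be chosen after seeing the data. The article does not say that non-achievers will be dropped, so the 79–86% is a consequence to guard against, not the announced plan.

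**Conclusion.** The point holds as one about support and sensitivity. The power of more than 95% belongs to an uncensored comparison of exactly seven versus five sessions. Seven is a prediction from a pilot that ended before any control reached the MCID. Five is a lower bound if the two responders took five days, since the third took longer. Calling the Aim 2 calculation conservative is not justified when 1.98 of the 2 assumed sessions are needed for 95% power.

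A reader might go further and say that the true power is 45%. The documents do not support that: no section states a control mean of six, and the same paragraph that mentions six sessions also allows for controls slower than eight. The supported statement is a range, from about 45% at six to near 100% at eight with non-achievers kept.

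These figures hold the SD at 1.5 and, in the main table, the combination mean at five, both from three people. They assume roughly normal session counts and a two-sided 0.05 test. The share of controls without a value (16% to 25%) follows from the plan's own mean and SD under that normal assumption.

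**What to change.** 1. In Sample size, replace the single Aim 2 figure with a range over the control mean, and stop describing the Aim 2 calculation as conservative.
2. In Statistical analysis, Hypothesis 2, make time to MCID, in sessions, the Aim 2 outcome from the start. Analyse it with a censored comparison such as the log-rank test, with participants who have not reached the MCID censored at session 8. This promotes the fallback in Study limitations to the main analysis.
3. Base the stated power on that test: with the combination at five sessions, SD 1.5 and 16 per arm, about 93% if controls average seven, about 73% at 6.5 and about 40% at six. Say that a slower control arm would raise it.

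The sample size, visits and treatments do not change. The cost is a less favourable stated power and an edit to the Hypothesis 2 text, which should be made before unblinded data are seen.
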